Matched cohort study in the Clinical Practice Research Datalink (CPRD), including participants who received the NHSHC with matched control participants. This design will enable a comparison of health outcomes between participants who had the health check with control participants who attend the same general practice but did not attend the NHSHC programme.

1. **Sample Size**

Based on Forster et al. study (8) (ISAC protocol 13-071A), we intend that this study will include the same 75,123 participants with a record of a complete NHSHC between 1st of April 2010 and 31st of March 2013 with follow-up data available three years after their health check (up to 31/3/2016), and the same 182,245 matched control participants who did not receive the check. All individuals were eligible for data linkage as discussed in section H.

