**Sample power calculation:**

Assuming that the background incidence of CHD is about 3 per 1,000 per year and the type 1 error rate is set at 0.05, if there are 75,000 health check participants and 182,000 control participants, there will be more than 90% power to detect a risk ratio of 0.85, for reduction of CHD incidence, over three years of follow-up.

1. **Data Linkage Required (if applicable)**

We have requested linkage to the Index of Multiple Deprivation data to test whether the outcomes of the NHS Health Checks differ across different socioeconomic status. We already have deprivation data obtained for protocol 13_071A but we will request all linked data again from the latest linkage Set (i.e. Set 12). This will ensure that we are working with the most accurate and consistent data (e.g. if a patient's postcode has been added or changed).

In addition, we are requesting ONS mortality data to enable cause of death analysis. We also plan to use integrated HES data to evaluate hospital admissions with ischaemic heart disease or stroke events. We are aware that a small number of patients may be eligible for linkage to IMD data but not eligible for linkage to the ONS mortality and inpatient HES data. This is because eligibility for linkage to IMD depends on the availability of a valid postcode, whereas eligibility for linkage to ONS and HES data depends on availability of a valid NHS number.

We will initially conduct the analysis using CPRD data only (the ‘unlinked analysis’). Subsequently, we will conduct a similar analysis using CPRD data together with linked data (the ‘linked analysis’). We will take into account the coverage period for the ONS mortality and inpatient HES data. Set 12 linkages provide ONS mortality and inpatient HES data through to 30/09/15, so the time period for the linked analysis will be restricted in comparison to the unlinked analysis. Patients who are not eligible for ONS and HES linkage will be excluded from the linked data analysis by restricting the study population to those eligible for all linkages. The loss of participants should not be large because the initial sample was drawn from linkage eligible participants.

1. **Study Population**

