The original sample was extracted from the October 2014 release of CPRD for 140,356 participants with a record of an NHS Health Check between 1 April 2010 and 31 March 2013, from 452 general practices in England. We restricted the sample to all 106,784 participants registered with 334 general practices with IMD 2010 quintile for England, linked via the participant postcode, at the lower super-output area level. We also excluded all patients who were ever treated with antihypertensive drugs (8531) or statins (1529) before the date of the check. We also excluded patients (4859) who did not have a full year of up to standard record before the date of the check and one patient whose check was after 31 March 2013. We also excluded patients with diabetes (227), coronary heart disease (2) or stroke (3) diagnosed before the check. There remained 91,618 participants who had a health check between 1 April 2010 and 31 March 2013, who had at least 12 months record, were never treated with antihypertensive drugs or statins, and were not diagnosed with diabetes, stroke or CHD before the check. For these 91,618 participants, eligible control participants were identified for 75,123 (82%) and these participants, and their matched controls, will be included in the present study.

1. **Selection of comparison group(s) or controls**

Control participants were selected if they were eligible for the NHS Health Checks but did not receive the check, they might have been invited to attend the Health Check, or not. The control participants were individually matched by general practice, gender and age with participants who received the Health Check.

1. **Exposures, Outcomes and Covariates**

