**Table 1: Case definitions for key measures:**

| **Condition** | **Read Codes** | **Therapy Codes** | **Test results** | **ICD-10 codes** |
| --- | --- | --- | --- | --- |
|  |  |  |  |  |
| **Ischaemic heart disease** | As listed in reference 9. | N/A | N/A | I20-I25 |
|  |  |  |  |  |
| **Stroke** | As listed in reference 10. | N/A | N/A | I60-I64 |
|  |  |  |  |  |
| **Diabetes mellitus** | As listed in Appendix 1. | BNF chapter 6.1.1 and 6.1.2 | HbA1c >=6.5% (48 mmol/mol) | E10-E14 |
|  |  |  |  |  |
| **Chronic kidney disease** | K05 and K06 codes | N/A | eGFR based on serum creatinine using CKD-EPI equation (11) | N18, N19 |
|  |  |  |  |  |

Secondary outcomes: CVD risk and CVD risk factors, including: smoking, BP, total cholesterol, HDL and BMI. Data on medication prescription for antihypertensive drugs, lipid-lowering drugs, antiplatelet drugs and nicotine replacement therapy will be analysed by recording drug codes to chapter subheadings in the British National Formulary (chapter 2 for CVD drugs).

1. **Data/ Statistical analysis**

The proportion of participants with values recorded for five risk factors (blood pressure, total cholesterol, HDL, BMI and smoking status) will be evaluated. Risk factor values will also be assessed. Changes over time in prescription of drugs for CVD risk management, including antihypertensive, lipid-lowering, antiplatelet and nicotine replacement therapy, will be evaluated.

The association between NHSHC and changes in CHD, stroke, diabetes and CKD clinical events will be examined using Cox hazard and Poisson regression models. Person-time approach will be adopted, where the start date is the date of the check. Hazard ratios will be estimated using Cox proportional hazards models and incident rate ratio using Poisson regression model. The proportional hazard assumptions will be tested. Linear mixed models will be used to study changes in continues outcomes (BP, cholesterol and BMI measurements). Follow-up will be censored if a control participant receives a health check at a later date. The effect of deprivation will be evaluated. Potential effect modification from deprivation category will be evaluated by testing for an interaction of health check status and deprivation category.

1. **Plan for addressing confounding**

To control for potential cofounders, model covariates will include age, gender, ethnicity and deprivation indices.

1. **Plan for addressing missing data**

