Recording of risk factor values is an outcome of importance in respect of evaluating NHS health checks. Prescriptions, clinical events and deaths that are not recorded will be presumed to be absent, because recording of these measures is expected to be complete.

1. **Limitations of the study design, data sources and analytical methods**

A randomised evaluation would provide the optimal study design but as health checks are part of a national policy, the present non-randomised design will offer an achievable study design. We expect a high level of completeness for recording of NHS health checks because use of mandated Read codes is used for reimbursement of practices. We acknowledge that there may be lack of standardisation of blood pressure measurements and recording of measures such as smoking and body mass index may be subject to misclassification. Use of diagnostic codes for CVD events varies between general practices and some clinical events are recorded with codes that lack precision.

1. **Patient or user group involvement (if applicable)**

Patients have not contributed to the development of this protocol but we have engaged with patients in our health check evaluation work and will be able to discuss the results of this study with patient groups.

1. **Plans for disseminating and communicating study results, including the presence or absence of any restrictions on the extent and timing of publication**

The results of this study will be reported in national public health events and we will also prepare peer review paper for publication. It will also contribute to a PhD thesis.

1. **References**

| Medcode | ReadCode | ReadTerm | Type |
| --- | --- | --- | --- |
| 506 | C100112 | Non-insulin dependent diabetes mellitus | 2 |
| 608 | 66A2.00 | Follow-up diabetic assessment | 2 |
| 711 | C10..00 | Diabetes mellitus | 2 |
| 758 | C10F.00 | Type 2 diabetes mellitus | 2 |
| 1038 | C100011 | Insulin dependent diabetes mellitus | 1 |
| 1323 | F420.00 | Diabetic retinopathy | 2 |
| 1407 | C10FJ00 | Insulin treated Type 2 diabetes mellitus | 2 |
| 1549 | C10E.00 | Type 1 diabetes mellitus | 1 |
| 1647 | C108.00 | Insulin dependent diabetes mellitus | 1 |
| 1682 | C101.00 | Diabetes mellitus with ketoacidosis | 1 |
| 1684 | 66A4.00 | Diabetic on oral treatment | 2 |
| 2340 | F381311 | Diabetic amyotrophy | 2 |
| 2342 | F372.12 | Diabetic neuropathy | 2 |
| 2378 | 66AJ.00 | Diabetic - poor control | 2 |

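### General practice is a matching factor but is missing from the stated Cox and Poisson models, so between-practice differences in CVD coding can bias the GP-coded CHD and stroke ratios

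*Protocol*

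**What the plan says.** The Protocol's section on selection of controls says that they were "individually matched by general practice, gender and age with participants who received the Health Check". The Sample Size section keeps the 75,123 checked people from the earlier study and "the same 182,245 matched control participants who did not receive the check". Under Study Population, 75,123 is 82% of the 91,618 checked people who qualified; no eligible control was found for the rest. The sample was drawn from 334 practices.

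Under Data/Statistical analysis, the event outcomes are to be modelled as follows: "Hazard ratios will be estimated using Cox proportional hazards models and incident rate ratio using Poisson regression model". The next section, on confounding, lists age, gender, ethnicity and deprivation as covariates. Neither practice nor matched set is named, and there is no mention of strata, frailty, conditional likelihood or clustered errors. Linear mixed models are named for the continuous outcomes only, without their random effects. The analysis section also ends a control's follow-up at a later health check.

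The limitations section concedes: "Use of diagnostic codes for CVD events varies between general practices". The missing-data section treats an unrecorded event as no event.

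**The concern.** Matching within practice allows checked and unchecked people to be compared under the same coding habits. The stated models keep two of the three matching factors (age and gender) and drop the third, which is the one tied to the coding variation that the protocol admits. Because an unrecorded event counts as absent, a practice that codes CHD or stroke less fully shows a lower event rate.

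Within a practice this affects both groups alike and cancels. In a pooled model it cancels only if each practice has the same relative weight among checked people and controls. Variable set sizes and control-only censoring both allow those weights to differ. The study is large enough for a bias of a few per cent to matter against the ratio of 0.85 that it is powered to detect.

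**Working it through.** **Inputs from the Protocol.** 75,123 checked and 182,245 controls (Sample Size); 91,618 eligible checked people (Study Population); "if there are 75,000 health check participants and 182,000 control participants", "the background incidence of CHD is about 3 per 1,000 per year", "the type 1 error rate is set at 0.05", three years and a risk ratio of 0.85 (Sample power calculation). Sidedness is not stated; two-sided is assumed. The documents do not give controls per set, the control ratio by practice or the spread of recorded event rates across practices. Values for these below are assumptions.

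**1. The plan's own figure.** Control risk is 3 × 0.003 = 0.009 and checked risk is 0.85 × 0.009 = 0.00765. Two-proportion power is 92.7%. Expected events are 182,000 × 0.009 = 1,638 and 75,000 × 0.00765 = 573.75, about 2,212 in all; the Schoenfeld formula gives 93.5%. The statement that "there will be more than 90% power to detect a risk ratio of 0.85" is reproduced and is not in dispute. The standard error of the log ratio is √(1/573.75 + 1/1,638) = 0.049, a 95% interval of about 0.77 to 0.93 around 0.85.

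**2. The control ratio.** 182,245/75,123 = 2.43. The mean is not a whole number, so sets are not all the same size. 91,618 − 75,123 = 16,495 checked people (18%) had no eligible control, which suggests that control supply was a limit.

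**3. When omitting practice causes bias.** For a practice, let r be controls per checked person (or control person-years per checked person-year, which is where control-only censoring enters) and λ the recorded event rate. With averages E taken over checked people and no true effect, the pooled ratio is

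B = E(λ) / [E(rλ)/E(r)] = E(r)·E(λ) / E(rλ).

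B equals 1 when r is constant, whatever the spread of λ, and also when r varies but is uncorrelated with λ. It departs from 1 only when the two move together across practices.

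**4. Two-type examples, all with mean ratio about 2.43.**

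| Assumed control ratios | Share of checked people in low-ratio practices | Recording difference | B, low-ratio practices record more | B, low-ratio practices record less |
|---|---|---|---|---|
| constant 2.43 | – | 2-fold | 1.00 | 1.00 |
| 2 vs 3 | 0.574 | 1.25-fold | 1.023 | 0.978 |
| 1 vs 3.86 | 0.5 | 1.1-fold | 1.029 | 0.973 |
| 1 vs 3.86 | 0.5 | 1.2-fold | 1.057 | 0.949 |
| 1 vs 3.86 | 0.5 | 1.3-fold | 1.083 | 0.929 |

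The last row written out: (1.3 + 1)/2 = 1.15; 1.15 / [(1.3 + 3.86)/4.86] = 1.083; reversed, 1.15 / [(1 + 1.3 × 3.86)/4.86] = 0.929.

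**5. Less schematic check.** A simulation used 334 practices, a ratio SD of about 1 and an SD of log recorded rate of 0.2 to 0.4. With no correlation between ratio and recording, the mean B was 1.00, with 95% ranges of 0.989–1.011 and 0.978–1.021. A correlation of −0.3 gave 1.02 to 1.05, and +0.3 gave 0.955 to 0.98. A correlation of ±0.6 gave about 0.91 to 1.10 at the extremes.

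**6. What a small bias does.** Under no effect the standard error is √(1/675 + 1/1,638) = 0.046. A bias of 1.02 shifts the test statistic by 0.0198/0.046 = 0.43 and raises the two-sided error rate from 5% to about 7%; a bias of 1.05 raises it to about 19%.

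**The case against.** Three objections have force.

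- The covariate list says what models will include, which need not be exhaustive. Strata and error structure are often left to a statistical analysis plan, and one may exist. That stands as a caution: the protocol does not say that the Cox model is unstratified. But it lists age and gender under its plan for confounding and omits practice, and nothing elsewhere suggests that practice is handled. An analyst following the text would leave it out.
- Omission alone does not produce bias, as step 3 shows. This stands in full. Varying set sizes are not enough either: the ratio, or the loss of control time, must track recorded rates between practices, and the documents do not show that. Variation caused by scarce age–gender groups within a practice would unbalance age and gender, which are adjusted for.
- Practice-clustered errors would change little, because exposure varies within practice. In the uncorrelated simulation the extra spread (SD about 0.01) moves a standard error of 0.049 to about 0.050, roughly 2%.

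A reader might go further and infer that all event ratios are biased. The admission covers CVD event codes only. Diabetes also uses prescriptions and HbA1c, CKD also uses eGFR, all-cause mortality does not depend on CVD coding, and the linked analysis adds HES and ONS sources. A reader might also infer that controls are scarcest where uptake is high, or that about half of the 15% effect is at risk. The first is plausible but no section reports uptake or ratio by practice. The second needs ratios of 1 and 3.86 with recording differing by 30% exactly along that split.

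**Conclusion.** The design and the stated analysis do not match: practice was used to select controls and is absent from the event models, while the protocol itself names a practice-level difference in CVD coding. With a non-constant control ratio and control-only censoring, this can bias the CHD and stroke ratios based on GP records. The unlinked analysis, which is done first, is the most exposed.

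Whether it does so, in which direction and by how much cannot be derived from the documents. The defensible range runs from no bias, through about 0.98 to 1.02 under a mild assumed split, to about 0.93 to 1.08 in a near-worst alignment. The last is not a strict bound, since larger assumed differences give more. Any error in the standard errors is probably small. This should be corrected, mainly because a better model is available at almost no cost; it does not show that the planned results would be wrong.

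**What to change.** State in the analysis section how the matching enters each model:

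- **Cox:** stratify by practice, keeping age and gender as covariates, or stratify by matched set.
- **Poisson:** use practice fixed effects or a conditional model.
- **Linear mixed models:** include practice and state the random effects.
- **Standard errors:** cluster on practice.
- **Reporting:** give the distribution of controls per set, and preferably control person-time per checked person-year by practice. That would show whether the route to bias is open.

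The cost is a few lines of specification. Practice was used for matching, so the identifier should already be held. Stratifying by matched set loses a little information; stratifying by practice loses almost none. In every scenario in the table the within-practice ratio is 1.00, so the change removes this source of bias without needing to know its size.

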**Objectives:**

1. To test the hypotheses that greater changes in CVD risk factors, CVD risk score and CVD risk management follow the NHS Health Check than are observed in control participants;
2. To test the hypothesis that all-cause mortality and the incidence of clinical events (new diagnoses of ischaemic heart disease, stroke, diabetes mellitus and chronic kidney disease) may be lower in participants who received NHS Health Checks than control participants;
3. To test the hypothesis that inequalities in the outcomes of Health Checks across deprivation category may be lower in NHS Health Check participants than in control participants.
4. **Background**

Cardiovascular disease is the leading cause of death worldwide and in the United Kingdom (1). Almost 155,000 deaths annually are caused by CVD in UK, accounting for more than a quarter of all deaths (2). Diabetes also is increasing in frequency, with four million people in UK living with diabetes, which is associated with serious complications leading to disability and premature mortality (3).The NHS Health Check (NHSHC) is a primary prevention programme that was introduced in England. The programme targets individuals aged 40 to 74 years, who have not yet developed CVD and are not treated for elevated risk, and estimates their risk of heart disease, stroke, type 2 diabetes, chronic kidney diseases and some forms of dementia (4). After identifying individuals at elevated risk, a personalised risk management intervention is provided. This programme provides an opportunity in terms of addressing multiple risk factors which, if successful, might reduce the risk of several diseases. Results from the Department of Health economic model suggested that the NHS Health Check could save 650 lives, and 1600 heart attacks and 4000 cases of diabetes could be prevented a year (5).

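### Objective 1 rests on mixed models of whatever risk-factor values are recorded: the check supplies attenders with an index reading, controls have only routine records, and unrecorded values have no stated method

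*Protocol*

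**What the plan says.** Objective 1 is to show that "greater changes in CVD risk factors, CVD risk score and CVD risk management follow the NHS Health Check than are observed in control participants". The Data/Statistical analysis section fixes the method for the measured factors: "Linear mixed models will be used to study changes in continues outcomes (BP, cholesterol and BMI measurements"). It gives no baseline definition, no measurement window and no rule for people without values.

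The exposed group consists of "participants with a record of a complete NHSHC between 1st of April 2010 and 31st of March 2013" (Sample Size), and person-time starts at the check. For the comparison group, "Control participants were selected if they were eligible for the NHS Health Checks but did not receive the check" (Selection of comparison group(s) or controls). Follow-up of a control stops at any later check.

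Recording is itself analysed: "The proportion of participants with values recorded for five risk factors (blood pressure, total cholesterol, HDL, BMI and smoking status) will be evaluated". The Plan for addressing missing data adds "Recording of risk factor values is an outcome of importance in respect of evaluating NHS health checks" and then gives a rule for other measures only: "Prescriptions, clinical events and deaths that are not recorded will be presumed to be absent, because recording of these measures is expected to be complete". The confounding section lists age, sex, ethnic group and deprivation as covariates. The limitations mention non-standard blood pressure readings and misclassification, but not recording that differs between the groups.

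**The concern.** The two arms enter the model by different routes. An attender's index reading comes with the exposure. A control's reading exists only if someone recorded it in routine care. Later readings are routine in both arms.

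A linear mixed model on recorded values is sound if recording depends only on the modelled covariates and on values already observed. The protocol neither states nor supports that assumption, and it treats recording as something the check may change. Its covariates offer little to make recording ignorable.

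At stake is the contrast that answers Objective 1 for blood pressure, cholesterol and BMI. The CVD risk score, which combines several factors, is likely to be at least as selected if only people with all values are used. With groups this large, a bias of 1 to 3 mmHg would look like a precise result.

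**Working it through.** The protocol gives no recording rates and no figure for these outcomes, so there is nothing to reproduce. Its one power statement concerns CHD incidence and is not involved. The check is therefore an illustration under assumptions, using systolic pressure with a true effect of zero.

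**1. Shift from selective recording.** Let the log-odds of recording rise by b per SD of the value, with recording probability p at the mean. To first order, the mean of recorded values exceeds the true mean by

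shift ≈ b × (1 − p) × SD.

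- Set A (assumed): between-person SD 14, within-person SD 10, so total SD = √(196 + 100) = 17.2; b from 0.2 to 0.4; p from 0.3 to 0.5. Smallest shift 0.2 × 0.5 × 17.2 = 1.7 mmHg; largest 0.4 × 0.7 × 17.2 = 4.8 mmHg.
- Set B (assumed): SDs 12 and 9, so total SD = √(144 + 81) = 15; b = 0.5; p = 0.4. Shift 0.5 × 0.6 × 15 = 4.5 mmHg.

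At index this shift applies to controls but not to attenders. Later it applies to whichever arm is selectively recorded.

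**2. What the mixed model returns.** The model borrows from repeated values within a person, so its bias is somewhat smaller than the raw shift. All attenders were measured at index. Set A had 8,000 per arm at years 0, 1 and 3. Set B had 1,500 against 3,600, three later occasions and 8 runs. Differences are attenders minus controls, in mmHg.

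| Assumed recording | False index difference | False change |
|---|---|---|
| B: unrelated to the value | −0.2 | +0.1 |
| B: controls value-dependent, attenders' later recording not | −2.9 | about 0 |
| B: attenders' later recording half as dependent as controls' | −3.1 | +1.3 |
| B: equally dependent | −3.4 | +2.6 |
| A: equally dependent | −1.6 to −4.1 | +1.2 to +3.1 |
| A: attenders' later recording unrelated to the value | not tabulated | +0.2 (50% recorded) to about +0.7 (30%) |

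A further null simulation of the same kind gave −1.8 to −3.9 at index. Its false change was +0.7 to +2.0 with equal dependence, and about zero or slightly negative when attenders' later recording was unrelated to the value.

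**3. Where the false change comes from.** In one set A run (30% recorded, b = 0.4), raw control means were 134.8, 134.4 and 134.0; attender means were 130.0, 134.7 and 134.4. The control gap at index, 134.8 − 130.0 = 4.8, matches step 1. Attenders rise by 134.4 − 130.0 = 4.4, while controls move by only 134.0 − 134.8 = −0.8. The artefact is attenders appearing to worsen as they go from complete to selected readings.

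**4. Against sampling error.** In set B the standard error of the change contrast was about 0.46 per run. The planned cohort of 75,123 and 182,245 is about 50 times larger in each arm (75,123/1,500 = 50.1; 182,245/3,600 = 50.6), so under the same assumptions the standard error is about 0.46/√50 = 0.065 mmHg. A false change of +1.3 would be about 20 standard errors.

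**The case against.** Several points on the other side stand.

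- **The mechanism is not documented.** A reader might infer that the model's missing-data assumption demonstrably fails here. The protocol gives no recording rates, consultation rates or reasons for measurement. Recording that depends on exposure alone does not invalidate a mixed model with exposure in it. If attenders are re-measured because the check reading was high, that reading is observed and a correctly specified model can use it. Bias in the change contrast needs dependence on values not seen.
- **Regression to the mean in controls is not the main driver.** A reader might expect high opportunistic control readings to fall back and mimic improvement. In set A the fitted control change at year 3 was only −0.6 to +0.1 mmHg.
- **Objective 1 cannot simply be answered either way.** It concerns change, so the index difference does not answer it. In sets A and B the material change bias runs against the check and can be near zero.
- **Eligibility removes some reasons for measurement.** Attenders had no prior antihypertensive or statin treatment and no diagnosed diabetes, CHD or stroke, and controls had to be eligible for a check.
- **Windows and imputation details often sit in an analysis plan**, which may exist unseen, and the proportion recorded is already to be reported. These are secondary outcomes.

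The last point does not dispose of the matter. This protocol has its own missing-data section, which names risk-factor recording and then leaves the values without a method, while the analysis section fixes the model.

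**Conclusion.** The point holds in conditional form. As written, the plan compares an arm with an index reading supplied by the exposure against an arm with routine readings only. It states no missing-data assumption and no sensitivity analysis for the values. If routine recording depends on the value, the index difference is biased, by about −1.6 to −4.1 mmHg systolic in these illustrations. The change contrast can be biased from about zero to about +3 mmHg against the check, depending mainly on how selectively attenders are recorded afterwards. These sizes rest on assumed recording of 30-50%, assumed slopes and assumed SDs. The protocol supplies none of them, so it does not show that the bias is present. Mortality and clinical events do not use these values and are unaffected.

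**What to change.** 1. Define the baseline value and the measurement windows identically in both arms, for example the last value before the index date within the same look-back, excluding the check reading.
2. Report the post-index contrast adjusted for that value and for consultation rate beside the planned mixed model, not in its place. In a null simulation this anchor cut the false contrast to about −0.1 to −0.6 mmHg when later recording was alike in both arms, but left −1.7 to −2.9 mmHg when it was not.
3. Add an analysis weighted by the inverse probability of measurement, or multiple imputation, with prescriptions, diagnoses and consultation rate as auxiliaries. State the missing-data assumption and show the percentage measured by arm and year beside each estimate.
4. Because step 3 also assumes that observed data explain recording, add a sensitivity analysis in which recording depends on the unseen value differently by arm.
5. Limit claims on risk-factor and CVD-score change to results that agree across these analyses.

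The cost is extra analysis of data already held, wider intervals, and a missing pre-index value for some people. Attenders were already required to have a full year of prior record, so a look-back of that length is available for them.
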